##### **2.9.5.2 Following Completion of the Study**

The study drug codes will only be available once all data collected will have been entered into the database for every participant and the data base has been finalised.

#### **2.9.6 Subject Withdrawal**

##### **2.9.6.1 Reasons for withdrawal**

The investigator may withdraw a patient from the study treatment procedures if the patient;

- Will be in violation of the protocol and/or
- Will experience an SAE that is related to the study drug and/or
- Will develop, during the course of the study, symptoms or conditions listed in the exclusion criteria and/or

- Will require a medication that is prohibited by the protocol

The investigator will also withdraw all participants from the study treatment if the study is terminated. Patients will be free to withdraw from the study at any time upon their request.

All the patients who will be withdrawn from the study will be followed up to completion of six months of follow up.

#### **2.9.6.2 Handling of withdrawals and losses to follow- up**

When a patient withdraws from the study, the reasons for withdrawal shall be recorded by the investigator on the relevant page of the CRF. Whenever possible, all patients who will withdraw from the study prematurely will continue to undergo scheduled visits for study assessments (follow-up).

Patients who will fail to return for study assessments will be contacted by the research team in an attempt to have them comply with the protocol. No contact after two documented phone calls to the patient and one to the next of kin will be considered a loss to follow up.

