In the subsequent monthly visits, patients will have medical history taken and clinical examination except height measurement (done only at baseline) done by the study doctor. In each of the monthly visits data on adherence to ARV drugs and compliance to study drugs, AEs, morbidity, mortality and co-medications will be collected. Additionally, patients will get their study medications refill and be counselled on adherence to ART and compliance to study drugs. In visit 0 and in all follow up visits, patients will also be asked to return to the clinics with their study drug boxes and ARV drug bottles in the next follow up visit for pill count. In addition to the aforementioned information, at months 2 and 3 blood samples for HIV viral load will be taken and also results for routine viral load test measurements for month 6 will be traced from the patients' files and/or medical records and will be included in the analysis. For CD4 count blood samples will be taken at 3 months and results for routine CD4 count measurements at month 6 will be traced from the patients' files and/or medical records and will be included in the analysis. For plasma levels of sCD14 and sP- selectin and for biomarkers of T cell activation and exhaustion blood samples will be taken at months 3 and 6. Blood samples for lipid profile, FBP, RFT and LFT will be taken only at 6 months. Urine samples will be taken from female participants for urine pregnancy test (UPT) during each monthly visit to check if they are pregnant.

|            | STUDY PERIOD                      | Screening
and
Randomizati
on | Study
Treatment | Follow- up    |         |         |         |
|------------|-----------------------------------|---------------------------------------|--------------------|---------------|---------|---------|---------|
|            | VISIT NUMBER                      | Visit 0                               | Visit 0            | Visits 1 – 7  |         |         |         |
|            | MONTH                             | Month 0                               | Month 0            | Months
1-6 | Month 2 | Month 3 | Month 6 |
| PROCEDURES | Informed consent                  | X                                     |                    |               |         |         |         |
|            | Demographic
information        | X                                     |                    |               |         |         |         |

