All-cause mortality will be defined as confirmed death of any cause with certification of death by medical practitioner or a verbal or telephone confirmation of death from a relative or friend. Clinical conditions associated with death will be determined by verbal autopsy and/or review of clinic and hospital records. Formal autopsies will not be conducted. Conditions will be defined as associated with death if they will be diagnosed within one month prior to or at time of death or were thought to be related to death after review of the medical records. More than one diagnosis will be possible for each death.

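### The loss-to-follow-up rule has no later vital-status check, so a death in a participant labelled lost may go unrecorded in all-cause mortality

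*Protocol*

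**What the plan says.** - **Loss rule (Protocol 2.9.6.2).** Participants who miss study assessments are contacted by the research team. The section then says: "No contact after two documented phone calls to the patient and one to the next of kin will be considered a loss to follow up". It sets no spacing between calls, no look at the clinic file and no later attempt.
- **Mortality outcome (1.6.3 item 7; 2.7; 2.11.7).** All-cause mortality is a secondary objective and outcome. The definition reads: "confirmed death of any cause with certification of death by medical practitioner or a verbal or telephone confirmation of death from a relative or friend".
- **When mortality is collected (2.10 and Table 2.1).** "In each of the monthly visits data on adherence to ARV drugs and compliance to study drugs, AEs, morbidity, mortality and co-medications will be collected".
- **Forms.** The Death Report Form (Appendix 4) is to be completed only when a participant's death is reported. The off-study page (Appendix 3, part I) lists loss to follow-up and death as separate reasons and mentions no later correction.
- **Withdrawn participants (2.9.6.1).** "All the patients who will be withdrawn from the study will be followed up to completion of six months of follow up". No matching sentence exists for participants labelled lost.
- **Month-6 laboratory results (2.10).** For viral load, "results for routine viral load test measurements for month 6 will be traced from the patients' files and/or medical records"; the same is said of CD4 count.
- **Safety reporting (2.12.1, 2.12.3, 2.12.4.1, 2.15.2).** A death is a serious adverse event, to be reported to the ethics committees within 24-72 hours. Adverse events are recorded until 30 days after the last dose. The DSMB reviews safety data.

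**The concern.** Of all outcomes in this trial, death is the one that the participant cannot report at a visit. Ascertainment therefore has to work for people who stop coming. Here the only active step written for them is three telephone calls, one of them to a relative. If the patient's phone is off and the relative misses that call, the label is loss to follow-up, and the protocol asks for nothing more.

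Two things are at stake. The mortality comparison may be short of deaths, and in a trial of newly diagnosed patients followed for six months the count is probably small enough for a few to matter. Secondly, a death within the adverse event recording window that sits under the loss label would not reach the ethics committees or the DSMB.

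This is not something to leave to an analysis plan. Analysis rules can say how to treat unknown vital status, but they cannot recover information that was never collected.

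**Working it through.** **1. Routes by which a death can enter the data, and whether each is active for a participant labelled lost**

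| Route | Where | Does the protocol require it once the participant is labelled lost? |
|---|---|---|
| Monthly visit | 2.10, Table 2.1 | No; the participant is not attending |
| Two calls to the patient, one to the next of kin | 2.9.6.2 | Already used up; that is how the label arises |
| Certification by a medical practitioner, or word from a relative or friend | Definitions item 7; 2.11.7 | Accepted if it arrives; nobody is told to seek it |
| Death Report Form | Appendix 4 | Starts only after a death has been reported |
| Clinic and hospital records | 2.11.7 | Used for the conditions associated with a death, so for deaths already known |
| Clinic file at month 6 | 2.10 | Opened for viral load and CD4 count; vital status is not mentioned |

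On the records row, the text reads: "Clinical conditions associated with death will be determined by verbal autopsy and/or review of clinic and hospital records". It describes how a known death is characterised, not how an unknown one is found. After the label, every remaining route to a death is passive.

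**2. How many participants could be in this position**

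The protocol's only loss figure is the 10% in its sample size calculation (2.13.1), so I first checked that calculation. Inputs: control proportion 0.75, intervention proportion 0.86, two-sided significance level 0.05, power 80%, allocation 1:1. With a pooled variance and no continuity correction, the mean proportion is (0.75 + 0.86)/2 = 0.805 and

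n = [1.960 × √(2 × 0.805 × 0.195) + 0.842 × √(0.75 × 0.25 + 0.86 × 0.14)]² / (0.86 − 0.75)²

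= [1.098 + 0.467]² / 0.0121 ≈ 202.5, so 203 per arm.

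Allowing for 10% loss: 203 / 0.90 = 225.6, so 226. The protocol states 227, which is reproduced within rounding.

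The expected number lost is then 454 × 0.10 = 45.4, about 45 in total, or 227 × 0.10 = 22.7, about 23 per arm.

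**3. How many deaths that means**

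Uncounted deaths = (number lost) × (share of the lost who died) × (share of those deaths not learned of by any passive route). Only the first term has a figure in the protocol, and that is a planning allowance. The second and third have none, so the product cannot be calculated.

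**4. Effect on the primary outcome**

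The sample size rests on viral load at week 8, so the stated 227 per arm does not change.

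**The case against.** The strongest reply is that 2.9.6.2 is a labelling sentence. It does not say that data collection stops, that later information is discarded, or that a death learned of afterwards is not counted. The mortality definition accepts "certification of death by medical practitioner or a verbal or telephone confirmation of death from a relative or friend", so a death does not hang on a single call. The study nurses, doctors and pharmacists are clinic staff, patients attend the same clinics monthly, and telephone tracing of non-attenders is budgeted (2.6, 2.9.1, 3.1, 3.2), so news of a death may well reach the study. Call spacing and end-of-study checks are also often written into site procedures.

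Most of this stands, and it limits the point: deaths may go unrecorded; the plan does not exclude them. What it does not supply is any instruction to look. The protocol chose to fix the tracing rule itself and fixed it at three calls.

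Three stronger readings are tempting and should not be made.

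- **That a month-6 viral load lying in the clinic file need not be sought for a lost participant.** Section 2.10 says month-6 results "will be traced from the patients' files and/or medical records and will be included in the analysis", with no exception for lost participants. At most, 2.9.6.2 could confirm this.
- **That a stated fraction of all deaths is missed.** One might assume that 5-20% of the 45 had died, giving 2-9 deaths, and divide by an assumed six-month mortality. The protocol supports neither rate, and the calculation also assumes that no such death is learned of by any other route.
- **That the mortality comparison is biased between arms.** This needs loss, or missed deaths among the lost, to differ by arm. Nothing in the protocol shows that it would, and the trial is double-blind.

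**Conclusion.** The point holds as a gap in ascertainment. Three calls are enough for the loss label, and no vital-status check follows. Since the other routes to a death depend on attendance or on someone volunteering the news, a death in a participant labelled lost may be missing from the all-cause mortality outcome and, if it falls within the recording window, from serious adverse event reporting.

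The group concerned is about 45 of 454 participants, if actual loss matches the 10% allowance and if all of it arises through this rule. The allowance was made for a week-8 endpoint, so loss over six months could differ. The number of deaths affected is unknown and cannot be derived from the protocol. The primary outcome and the sample size are untouched. This is a worthwhile, inexpensive improvement to a secondary and safety outcome, not a fault that undermines the trial.

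**What to change.** Amend 2.9.6.2 as follows:

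1. Keep the two calls to the patient and one to the next of kin, but let them trigger a provisional loss only.
2. At each such participant's scheduled month-6 date, check the clinic (CTC) file for attendance, transfer or death, and make one further call to the patient and one to the next of kin to establish vital status.
3. If either source shows a death, change the off-study reason to death and complete the Death Report Form.
4. State that the month-6 tracing of viral load and CD4 count in 2.10 also applies to these participants.

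At the planned loss rate the cost is about 45 file checks and up to 45 × 2 = 90 calls. The files are already to be opened at month 6, and telephone tracing has its own budget line (3.1), so the burden is a little site time. One limit remains: a death first found at month 6 would be too late for the 24-72 hour reporting target, so the check restores the outcome and a late safety report, not a timely one.

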#### **2.9.6.3 Replacements**

There will be no replacement of patients who will discontinue the study by further recruitment to maintain the required minimum sample size.

#### **2.9.7 Trial Closure**

The trial will be closed once the last patient to be enrolled into the study has completed their last follow up visit.

#### **2.9.8 Continuation of therapy**

No study medication will be issued to a patient after the final treatment day (6 months of study medication use). Patients will continue with their HIV/ AIDS standard treatments.

### **2.10 Study Visits and Procedures schedule**

There will be a total of 7 visits for each patient. At visit 0, patients attending CTCs at each site will be informed about the proposed study and will be invited to participate by the study nurses and doctors. Informed consent will be obtained from the patients by the study nurse who is an employee at the respective CTC. After the patient has given an informed consent, he/she will then be asked

to provide their demographic information. For all the male patients, confirmation of eligibility will be after the demographics while for female patients after the medical history they will be asked to provide urine for pregnancy test. A positive test will exclude them from the study. Once one is found eligible, they will be consecutively enrolled into the study followed by medical history and a clinical examination including blood pressure, height and weight measurements. Once the clinical examination is complete, participants will be randomized to the treatment groups and then blood samples will be taken for baseline investigations before initiation of the ARV drugs and the study drugs. The baseline investigations will include RFT, LFT, CD4 counts and FBP which are routinely taken before initiation of ART. In addition, specifically for this study, blood samples for viral load, lipid profile, plasma levels of sCD14 and sP- selectin, biomarkers of T cell activation and exhaustion will be taken at baseline.

In the subsequent monthly visits, patients will have medical history taken and clinical examination except height measurement (done only at baseline) done by the study doctor. In each of the monthly visits data on adherence to ARV drugs and compliance to study drugs, AEs, morbidity, mortality and co-medications will be collected. Additionally, patients will get their study medications refill and be counselled on adherence to ART and compliance to study drugs. In visit 0 and in all follow up visits, patients will also be asked to return to the clinics with their study drug boxes and ARV drug bottles in the next follow up visit for pill count. In addition to the aforementioned information, at months 2 and 3 blood samples for HIV viral load will be taken and also results for routine viral load test measurements for month 6 will be traced from the patients' files and/or medical records and will be included in the analysis. For CD4 count blood samples will be taken at 3 months and results for routine CD4 count measurements at month 6 will be traced from the patients' files and/or medical records and will be included in the analysis. For plasma levels of sCD14 and sP- selectin and for biomarkers of T cell activation and exhaustion blood samples will be taken at months 3 and 6. Blood samples for lipid profile, FBP, RFT and LFT will be taken only at 6 months. Urine samples will be taken from female participants for urine pregnancy test (UPT) during each monthly visit to check if they are pregnant.

|            | STUDY PERIOD                      | Screening
and
Randomizati
on | Study
Treatment | Follow- up    |         |         |         |
|------------|-----------------------------------|---------------------------------------|--------------------|---------------|---------|---------|---------|
|            | VISIT NUMBER                      | Visit 0                               | Visit 0            | Visits 1 – 7  |         |         |         |
|            | MONTH                             | Month 0                               | Month 0            | Months
1-6 | Month 2 | Month 3 | Month 6 |
| PROCEDURES | Informed consent                  | X                                     |                    |               |         |         |         |
|            | Demographic
information        | X                                     |                    |               |         |         |         |
|            | Medical history                   | X                                     |                    | X             |         |         |         |
|            | Clinical
examination           | X                                     |                    | X             |         |         |         |
|            | Height
measurement             | X                                     |                    |               |         |         |         |
|            | Weight
measurement             | X                                     |                    | X             |         |         |         |
|            | Blood    pressure
measurements | X                                     |                    | X             |         |         |         |
|            | Urine   pregnancy
test         | X                                     |                    | X             |         |         |         |
|            | Confirm eligibility               |                                       |                    | X             |         |         |         |
|            | Randomization                     | X                                     |                    |               |         |         |         |
|            | CD4 count                         | X                                     |                    |               |         | X       | X       |
|            | Viral load                        | X                                     |                    |               | X       | X       | X       |
|            | FBP                               | X                                     |                    |               |         |         | X       |

|                   |                                     |          |          |          |  |          |                      |
|-------------------|-------------------------------------|----------|----------|----------|--|----------|----------------------|
|                   | RFT                          | X |          |          |  |          | X             |
|                   | LFT                          | X |          |          |  |          | X             |
| PROCEDURES | Lipid profile                | X |          |          |  |          | X
X |
|                   | sCD14, sP-selectin           | X |          |          |  | X | X             |
|                   | CD38, HLA-DR, PD-1           | X |          |          |  | X | X             |
|                   | Study drug dispensing        |          | X | X |  |          |                      |
|                   | Adherence to ART check       |          |          | X |  |          |                      |
|                   | Compliance to ASA check      |          |          | X |  |          |                      |
|                   | Morbidity check              |          |          | X |  |          |                      |
|                   | Adverse event check          |          |          | X |  |          |                      |
|                   | Mortality check              |          |          | X |  |          |                      |
|                   | Concomitant medication check |          |          | X |  |          |                      |

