## **2.9 Subject enrolment and randomization**

### **2.9.1 Recruitment**

Subjects will be recruited from CTCs in Dar es Salaam. Patients attending CTCs at each site will be informed about the proposed study at the CTCs and will be invited to participate by the study nurses and doctors (who are also CTC staff). Prior to performing any study specific procedure (including screening procedures to determine eligibility), a signed consent form will be obtained for each subject once they have been diagnosed to be HIV- infected. The consent form will describe the purpose of the study, the procedures to be followed, and the risks and benefits of participation. The study nurse who will be part of the CTC staff and well informed of the study protocol, will conduct the informed consent discussion and will check that the subject comprehends the information provided and answer any questions about the study. Should there be an issue raised by the patients that the study nurse cannot address, the study doctor will be at hand to assist. Consent will be voluntary and free from coercion. The study nurse that will have conducted the consent discussion will also sign the informed consent form. A copy of the consent form will be given to the subject and the fact that the subject has been consented to the study will be documented in the subject's record. Then, a screening number will be given to the already consented patient by the study nurse. The patient will be attended by the study doctor and assessed for eligibility. When all the inclusion and exclusion criteria have been addressed and the eligibility of the subject confirmed, the subject will be consecutively recruited into the study and will be given a study number by the study doctor. The patient will go with the study number to the pharmacy and show it to the study pharmacist. The study pharmacist will give a box containing the study drugs according to the study number and the randomization schedule.

On average, 10 patients will be registered for care per week at each study site making 20 patients per week and 80 patients per month. Therefore, for 454 patients the recruitment is expected to last

for at least 6 months. Reasons for ineligibility for patients and reasons for non-participation of eligible subjects will be documented.

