### **2.9.2 Eligibility Criteria**

Patients will be assigned to a randomized study treatment only if they meet all of the inclusion criteria and none of the exclusion criteria.

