| Is the participant on current or previous regular use of ASA at any dose or current use of another NSAID?                                                       |  |  |
| Is the participant on current or long term use of oral corticosteroids?                                                                                         |  |  |

III: Screening Investigations:

1. Was UPT done? 1. YES\_\_\_\_\_ Results: \_\_\_\_\_ (Positive/Negative/Not Applicable)  
2. No\_\_\_\_\_ Reason\_\_\_\_\_
2. Was serum creatinine done? 1. YES\_\_\_\_\_ Results: Serum creatinine\_\_\_\_\_ mg/dL  
2. No\_\_\_\_\_ Reason\_\_\_\_\_

IV: Inclusion criteria

*All answers to questions 1-6 must be **YES** for the subject to be eligible.*

| Serial No | QUESTION                                                                    | RESPONSE |    |
|-----------|-----------------------------------------------------------------------------|----------|----|
|           |                                                                             | YES      | NO |
| 1.        | Has the participant given an informed consent?                              |          |    |
| 2.        | Is the participant HIV- infected?                                           |          |    |
| 3.        | Is the participant ARV drugs naïve?                                         |          |    |
| 4.        | Is the participant 18 years old or above?                                   |          |    |
| 5.        | Is the participant attending CTC at MbagalaRangiTatu or Mwananyamala |          |    |
| 6.        | Is the participant residing in Dar es Salaam?                               |          |    |

V: Exclusion criteria

All answers to questions 1 -9 must be **NO** for the subject to be eligible.

| Serial No | QUESTION                                                                                                                                                        | RESPONSE |    |
|-----------|-----------------------------------------------------------------------------------------------------------------------------------------------------------------|----------|----|
|           |                                                                                                                                                                 | YES      | NO |

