| 1.        | Does the participant have history of intolerance or allergy to ASA or any ASA containing products or NSAIDs or celecoxib or other salicylates or sulphonamides? |          |    |
| 2.        | Is the participant asthmatic?                                                                                                                                   |          |    |
| 3.        | Does the participant have any bleeding diatheses?                                                                                                               |          |    |
| 4.        | Does the participant have active or history of peptic ulceration or gastrointestinal bleeding within the last year?                                             |          |    |
| 5.        | Is the participant on antithrombotic/ antiplatelet therapy?                                                                                                     |          |    |
| 6.        | Is the participant on current or previous regular use of ASA at any dose or current use of another NSAID?                                                       |          |    |
| 7.        | Is the participant on current or long term use of oral corticosteroids?                                                                                         |          |    |
| 8.        | Is the participant's urine pregnancy test positive?                                                                                                             |          |    |
| 9.        | Does the participant have history of moderate or severe renal impairment, with eGFR < 45 ml/ min/ 1.73 m                                            |          |    |

VI: SELECTION OF PARTICIPANTS INTO THE TRIAL

1. Is the participant eligible? \_\_\_\_ (YES/NO) If no why? \_\_\_\_\_
2. Is the participant selected into the study? \_\_\_\_ (YES/NO) If no why?  
\_\_\_\_\_
3. Participant's study number \_\_\_\_\_
4. Investigator's signature \_\_\_\_\_ Date \_\_\_\_/\_\_\_\_/\_\_\_\_

**BASELINE INFORMATION FORM AFTER SELECTION INTO THE STUDY** (*To be filled in on Visit 0*)

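### The exclusion criteria in 2.9.2.2 and on the Appendix 2 form disagree, and 2.10 randomises without a renal result

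*Protocol*

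**What the plan says.** **Exclusion lists.** Protocol 2.9.2.2 excludes severe renal disease (eGFR below 30 ml/min/1.73 m²), active or past peptic ulcer disease with no time limit, and intolerance or allergy to aspirin or aspirin products. The Appendix 2 form requires NO to every exclusion question. It puts the renal limit at eGFR below 45 and asks about peptic ulceration or GI bleeding with the past year as a window. It also asks about regular aspirin use, current or previous, and about allergy to NSAIDs, celecoxib, other salicylates and sulphonamides.

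**Order of steps.** Section 2.9.2 states the rule: "Patients will be assigned to a randomized study treatment only if they meet all of the inclusion criteria and none of the exclusion criteria". Section 2.9.1 agrees. The study number follows "When all the inclusion and exclusion criteria have been addressed and the eligibility of the subject confirmed", and then "The study pharmacist will give a box containing the study drugs according to the study number and the randomization schedule".

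Section 2.10 describes Visit 0 differently. On eligibility it says "For all the male patients, confirmation of eligibility will be after the demographics"; women also have a urine pregnancy test. Enrolment, history and examination follow, and then "Once the clinical examination is complete, participants will be randomized to the treatment groups and then blood samples will be taken for baseline investigations". On what that blood is for: "The baseline investigations will include RFT, LFT, CD4 counts and FBP which are routinely taken before initiation of ART".

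**Creatinine on the form.** Appendix 2 has two entries. Among the screening investigations, before the study number, it asks "Was serum creatinine done" and accepts No with a reason. A second entry, for renal function tests, comes under "BASELINE INFORMATION FORM AFTER SELECTION INTO THE STUDY".

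**The concern.** Eligibility should have one answer per patient. Here it depends on which page is used. A patient with eGFR between 30 and 44 is eligible under 2.9.2.2 and excluded by the form. The reverse may hold for an ulcer more than a year old. A patient with recent GI bleeding, previous regular aspirin use or a sulphonamide allergy is stopped by the form, while 2.9.2.2 does not name any of these. The protocol's own Background names GI bleeding as a risk of aspirin, so the ulcer and bleeding items matter directly to safety.

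The visit narrative adds a second problem. A site following 2.10 as written could allocate and dispense aspirin before anyone has seen the creatinine result that decides a renal exclusion. For men, the text also places confirmation of eligibility ahead of the medical history that the ulcer, asthma and allergy exclusions need.

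**Working it through.** **Step 1. The lists side by side**

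| Item | 2.9.2.2 | Appendix 2 form |
|---|---|---|
| Renal | eGFR < 30 | eGFR < 45 |
| Peptic ulcer | active or past, no time limit | active or past, one-year window in the same question |
| GI bleeding | not named | named, one-year window |
| Allergy or intolerance | aspirin and aspirin products | also NSAIDs, celecoxib, other salicylates, sulphonamides |
| Previous regular aspirin use | not listed | excludes |

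The ulcer question has two readings. If the window covers both conditions, older ulcers pass the form but not 2.9.2.2. If it covers bleeding only, the form adds a bleeding exclusion that 2.9.2.2 does not name. The lists differ either way. Form items on drugs that 2.9.2.2 reaches through Appendix 5 are left out of this comparison.

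**Step 2. What the two renal limits mean in creatinine**

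Appendix 7 gives eGFR = 175 × Scr^(−1.154) × age^(−0.203) × 0.742 (if female) × 1.212 (if Black), with Scr in mg/dL. Write K for everything except the creatinine term. Then Scr = (K / eGFR)^(1/1.154). The ages and the use of the Black coefficient are assumptions.

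For a woman aged 40, K = 175 × 0.4729 × 0.742 × 1.212 = 74.43.
- Limit 45: (74.43/45)^(1/1.154) = 1.547 mg/dL
- Limit 30: (74.43/30)^(1/1.154) = 2.198 mg/dL

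For a man aged 40, K = 175 × 0.4729 × 1.212 = 100.30.
- Limit 45: 2.003 mg/dL
- Limit 30: 2.846 mg/dL

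Creatinine range (mg/dL) in which the two lists give opposite decisions:

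| Age | Women | Men |
|---|---|---|
| 18 | 1.78 to 2.53 | 2.31 to 3.28 |
| 25 | 1.68 to 2.39 | 2.18 to 3.09 |
| 40 | 1.55 to 2.20 | 2.00 to 2.85 |
| 60 | 1.44 to 2.05 | 1.87 to 2.65 |

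Checks in the forward direction: 1.8 mg/dL in the woman aged 40 gives 74.43 × 1.8^(−1.154) = 74.43 × 0.5075 = 37.8. A value of 2.4 mg/dL in the man aged 40 gives 100.30 × 0.3641 = 36.5. Both patients are eligible under 2.9.2.2 and below the form's limit.

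**Step 3. Is a renal result available before allocation?**

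- 2.10: confirm eligibility, enrol, history and examination, randomise, then draw blood that includes the renal function test.
- 2.11.6: renal function is tested at the MUHAS Clinical Research Laboratory after motorcycle transport, and the serum is frozen at −80 °C until analysis. Nothing assures a result on the same day.
- Appendix 2: a screening creatinine comes before the exclusion questions and the study number, but it may be marked as not done.

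Section 2.10 may therefore be omitting the screening creatinine rather than deliberately reversing the order. As written, it still conflicts with 2.9.1, 2.9.2 and the form.

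**The case against.** The strongest reply is that the form is the working instrument and already provides the control. The study doctor assesses eligibility, every exclusion answer must be NO, creatinine is listed under screening, and the pharmacist dispenses only against the study number. On renal function, aspirin use and allergies the form is the stricter list, so a mismatch there leads to exclusion and not to exposure. Appendix 6 defines regular aspirin use and current NSAID use, which are the form's terms and suggest that the form is the intended version. Section 2.10 would then be a loose summary. Its randomisation sentence goes on to place the blood draw before ARV and study drugs are started, and Table 2.1 shows the renal test in the screening and randomisation column. On ulcers, the one-year window may attach to bleeding alone, and 2.11.2 asks for ulcer and bleeding history without a window.

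Much of this stands as mitigation. The form is a partial control, and the looser ulcer reading is only one of two. It does not remove the fault. The two eGFR limits cannot both be right. Neither Appendix 6 nor 2.11.2 reconciles the lists. Drawing blood before the first dose fixes the time of the sample, not the arrival of a result, and 2.11.6 freezes that serum. The form also lets a creatinine go undone with a reason given.

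**Conclusion.** The point holds and should be fixed. Sections 2.9.2.2 and Appendix 2 set incompatible exclusion rules, and 2.10 describes randomisation with no renal result in hand, against 2.9.1, 2.9.2 and the form's own screening section.

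The renal disagreement covers every patient with eGFR from 30 up to 45. The creatinine bands above translate that interval through Appendix 7; they do not estimate how many patients are affected. The protocol gives no distribution of renal function, ulcer history or prior aspirin use, so that number is unknown. The conclusion on the lists needs no assumption beyond the text. The conclusion on 2.10 rests on reading it as written, allowing that it may omit a step rather than reverse one. The consequence is for participant safety and for consistent eligibility decisions. No bias, loss of power or change in sample size follows.

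**What to change.** 1. Make 2.9.2.2 and the Appendix 2 exclusion questions one identical list. The sponsor's clinicians should choose one eGFR limit (30 or 45) and one ulcer and GI-bleeding window, and decide whether previous regular aspirin use and the additional allergies exclude.
2. Rewrite 2.10 so that medical and drug history, the pregnancy test for women, and an available creatinine or eGFR result all precede confirmation of eligibility and issue of the study number. The routine pre-ART renal function test or the form's screening creatinine can serve.
3. State in 2.11.6 that this sample is analysed promptly and not frozen.
4. Do not allow a study number when creatinine is marked as not done.

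**Cost.** One amendment to 2.9.2.2, 2.10, 2.11.6 and Appendix 2. The budget funds 908 renal function tests (2 × 454) at 2,860 Tshs, and 908 × 2,860 = 2,596,880 Tshs reproduces its line. That leaves none for screen failures.
- Routine test moved ahead of randomisation: extra tests assumed at 5% to 20% of 454, which is 23 to 91 tests, or 65,780 to 260,260 Tshs.
- Separate screening creatinine for all 454, priced as a renal function test (an assumption): 454 × 2,860 = 1,298,440 Tshs, which is 1.05% of 123,722,026.40 Tshs.

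The practical cost is time. If the screening sample also goes to the off-site laboratory, waiting for the result may split Visit 0 or delay the start of ART by a turnaround time that the protocol does not state.
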